**Data collection and follow-up for withdrawn subjects**

Participants will be followed up at 6 weeks, 3 months (over the phone) and 6 and 12 months unless they explicitly want no further contact.

### STATISTICAL CONSIDERATIONS

**Primary Endpoint Efficacy Analysis**

Change in weight from baseline at 6 months after enrolment into the study.

**Secondary Endpoint Efficacy Analysis**

Secondary analyses will also be conducted at 6 weeks and 3 and 12 months months after enrolment into the study.

**Safety Endpoints**

There are no safety endpoints for this trial.

**Statistical Analysis**

Analyses will be undertaken after the last participant has completed the 6-month follow-up. ITT analysis will be conducted as the primary outcome, with participants lost to follow-up included as achieving no weight loss. 'Last-weight-carried-forward' imputation and 'completers only' analysis limited to participants who provide follow-up data are reported as sole outcomes in many weight loss trials. To allow comparison across studies, we will conduct such analyses as well.

Weight change will be analysed by analysis of variance (ANOVA) with comparisons between all pairs of the three groups.

We shall also examine the effect of age, socioeconomic grouping, BMI at baseline and gender on weight loss and include any univariately significant variables in an analysis of covariance (ANCOVA) of weight change alongside study arm allocation. We shall assess, via interaction, the moderator effects of these variables on weight loss.

We will also calculate the proportion of randomised participants who achieved at least 5% weight loss and odds ratios for percentage weight change will be analysed via logistic regression.

Further to this, we will report group sessions attended in the 5-2 BS arm, and adherence to 5-2 in both 5-2 arms, together with 5-2 ratings; and report adherence to and evaluation of elements of the advice provided in SH arm, concerning changes in diet and exercise levels. IPAQ and FFDBQ scores in the three study arms will be compared using ANOVA.

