### SUMMARY/SYNOPSIS

| **Short Title** | 5-2 Study |
| --- | --- |
| **Methodology** | Randomised controlled trial |
| **Study Centre** | Health and Lifestyle Research Unit, [name] |
| **Objectives/Aims** | 1. Determine the effectiveness of the 5-2 diet combined with multi-session group support compared to the 5-2 diet delivered in a self-help format and to standard advice on diet and physical activity, in terms of weight loss at 6 weeks, 3 months (self-reported), 6 and 12 months 2. Explore predictors of, and barriers and facilitators to, adherence to the 5-2 diet. |
| **Number of Participants** | 300 |
| **Main Inclusion Criteria** | Adults, aged 18 years and older, with a BMI ≥30kg/m2, or BMI≥28kg/m2 with comorbidities |
| **Statistical Methodology and Analysis (if applicable)** | The primary analysis will compare weight loss between the three groups at 6 months, adjusting for baseline weight. We propose to implement a strict intention to treat (ITT) analysis as our primary outcome, with participants lost to follow-up included as achieving no weight loss. |
| **Study Duration** | 30 months |

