**Study Design / Plan – Study Visits**

**Study Scheme Diagram**

| **Recruitment**  Potential participants will contact the study team via phone/email after seeing study advertisements in local newspapers and on the internet. Staff will provide information about the study and if the potential participant is interested, they will be screened. If eligible, they will receive an appointment for the baseline visit and sent the Participant Information Sheet (PIS) and booking confirmation. The phone call will take up to 20 minutes. | | | | | | | |
| --- | --- | --- | --- | --- | --- | --- | --- |
|  |  | | |  | |  |  |
| **Baseline visit**  Participants will receive information about the study and provide written informed consent; baseline data will be obtained including weight, height, blood pressure and demographic details; eating and physical activity questionnaires will be completed.  Participants will be randomised to 5-2 Behavioural support, 5-2 self-help, or standard advice arms. | | | | | | | |
|  | |  |  | |  | |  |
| **5-2 self-help (5-2 SH)**  **(N=100)**  20 minute session on the 5-2 plan, a written guide on how to use it with recommendations for internet and other resources and a leaflet listing local resources for exercise. | |  | **5-2 plus group support (5-2 GS) (N=100)**  Participants receive the same materials as in the 5-2 self-help condition and attend 6 weekly group support sessions. | |  | **Standard advice self help (SH) (N=100)**  20-minute session  on healthy eating and physical activity and the British Heart Foundation guides Facts Not Fads and Get Active, Stay Active plus the NHS Change  4 Life series of booklets and a leaflet listing local resources for exercise. | |
|  | |  |  | |  |  | |
| **6 week follow up**  Measurement of weight and blood pressure; recording of any concomitant weight management treatments; adherence to and ratings of 5-2 diet | |  | **6 week follow up**  Measurement of weight and blood pressure; recording of any concomitant weight management treatments; adherence to and ratings of 5-2 diet | |  | **6 week follow up**  Measurement of weight and blood pressure; recording of any concomitant weight management treatments; adherence to and ratings of advice components | |
|  | |  |  | |  |  | |

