**Sample Size**

In this early phase primary research, we opted for a pragmatic sample size

achievable economically and quickly but large enough to provide reasonable confidence intervals on the key estimates. We aim to randomise 100 participants in each study arm.

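### The synopsis and the statistics section do not state the same primary model: one adjusts for baseline weight, the other names no such covariate

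*Protocol*

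**What the plan says.** Two places in the protocol describe the analysis of the primary outcome.

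- **Summary/Synopsis**, row on statistical methodology: "The primary analysis will compare weight loss between the three groups at 6 months, adjusting for baseline weight".
- **Statistical Considerations, Statistical Analysis**: "Weight change will be analysed by analysis of variance (ANOVA) with comparisons between all pairs of the three groups". This sentence names neither a covariate nor a time point.

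The Statistical Analysis section then adds a further step: "We shall also examine the effect of age, socioeconomic grouping, BMI at baseline and gender on weight loss", after which the team will "include any univariately significant variables in an analysis of covariance (ANCOVA) of weight change alongside study arm allocation".

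The endpoint itself is defined under Primary Endpoint Efficacy Analysis as "Change in weight from baseline at 6 months after enrolment into the study". The rule for missing data agrees in both places: "ITT analysis will be conducted as the primary outcome, with participants lost to follow-up included as achieving no weight loss". Weight is recorded at the baseline visit, where "baseline data will be obtained including weight, height, blood pressure and demographic details". On size, the Sample Size section says "We aim to randomise 100 participants in each study arm". It gives no SD, correlation, alpha or power.

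**The concern.** A comparison of weight change adjusted for baseline weight and a plain ANOVA of weight change are different models. They give different point estimates, standard errors and p-values from the same data. The protocol attaches the word primary to the first. Its statistics section, where an analyst would look for the specification, describes the second. Nothing in the document says which governs.

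The screened ANCOVA adds a third candidate, whose covariates depend on the data. If the choice is left open until the 6-month data are in, it can be made with the results in view, and each answer could be defended as the planned one.

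**Working it through.** **Do the passages describe the same model?**

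| Place | Outcome | Covariates |
|---|---|---|
| Synopsis | weight loss at 6 months | baseline weight, fixed in advance |
| Statistics section, ANOVA sentence | weight change | none named |
| Statistics section, further ANCOVA | weight change | whichever of age, socioeconomic grouping, baseline BMI and gender are univariately significant |

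Three readings that might reconcile them fail.

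1. *Adjusting means only subtracting the baseline.* The synopsis outcome is already a loss, and the endpoint is already a change. Adjusting that change for baseline weight is a second operation.
2. *ANOVA is used loosely and includes the covariate.* The same section uses the term ANCOVA when covariates enter.
3. *The further ANCOVA supplies the adjustment.* It is an additional step, baseline weight is not a candidate, and BMI is a different variable that enters only if significant.

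**How much could it matter?**

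The protocol supplies n = 100 per arm and no variances, so the rest is assumed: SD of change 5 kg, SD of baseline weight 16 kg, and correlation r of change with baseline from -0.1 to -0.4.

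- SE of the baseline difference between two arms: 16 × √(2/100) = 2.26 kg. Twice this is 4.53 kg.
- SE of the unadjusted difference in change: 5 × √(2/100) = 0.707 kg.
- Slope of change on baseline, in size: |r| × 5/16.
- Shift in the estimate: slope × imbalance.
- Adjusted SE: 0.707 × √(1 − r²).

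| r | Slope (kg/kg) | Shift at 1 SE imbalance | Shift at 2 SE imbalance | Adjusted SE | SE lower by |
|---|---|---|---|---|---|
| -0.1 | 0.031 | 0.07 kg | 0.14 kg | 0.704 kg | 0.5% |
| -0.3 | 0.094 | 0.21 kg | 0.42 kg | 0.675 kg | 4.6% |
| -0.4 | 0.125 | 0.28 kg | 0.57 kg | 0.648 kg | 8.3% |

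In units of the unadjusted SE, the shift is |r| times the number of SEs of imbalance: 0.1 to 0.4 SE at 1 SE, and 0.2 to 0.8 SE at 2 SE.

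**A second parameterisation.** Assume baseline SD 18 kg, change SD 6 kg, and follow-up weight = b × baseline + error. The unadjusted SE is 6 × √(2/100) = 0.849 kg. The adjusted SE is √(36 − (b − 1)² × 18²) × √(2/100). The SD of the gap between the two estimates is about |b − 1| × 18 × √(2/100). For each b, 5,000 two-arm comparisons were simulated with a true difference of 2 kg, and the decisions at p < 0.05 were compared.

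| b | Implied r | Adjusted SE | SD of gap | Decisions that differ |
|---|---|---|---|---|
| 0.98 | -0.06 | 0.847 kg | 0.05 kg | 2.1% |
| 0.95 | -0.15 | 0.839 kg | 0.13 kg | 3.9% |
| 0.92 | -0.24 | 0.824 kg | 0.20 kg | 7.2% |

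**A third view.** If baseline and follow-up weight have equal variance and correlation ρ, the variance ratio of adjusted to unadjusted is (1 + ρ)/2. That is 0.90 at ρ = 0.80 and 0.99 at ρ = 0.98, so the SE falls by 5.1% and 0.5%.

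**The case against.** The best defence is that the two passages differ in detail rather than conflict. The statistics section never calls its ANOVA unadjusted and never labels that sentence the primary analysis. The only sentence that does specify the primary analysis is in the synopsis, and it names the adjustment. A full model is also commonly left to a SAP, which is not shown. This does not remove the problem. The section separates ANOVA from ANCOVA by name, and a SAP that chose either model would sit awkwardly with one of the two statements.

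The objections on size do stand.

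- Under randomisation the unadjusted comparison of change is unbiased, and its SE already allows for chance imbalance. Adjustment brings conditional balance and some precision. It does not correct a bias.
- A 2-SE imbalance arises in only about 5% of randomisations for a given pair of arms, so the right-hand shift column is a tail case.
- Counting participants lost to follow-up as having no weight loss would weaken the correlation of change with baseline if loss is unrelated to baseline weight. That would shrink the effect further.
- The trial is described as early phase, and its size was chosen pragmatically. No power claim hangs on this choice.

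A reader might infer that the statistics section throws away the baseline measurement. The documents do not support that. The outcome is change from baseline, so baseline weight is used by subtraction in every participant. What is missing is baseline weight as a covariate.

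**Conclusion.** The point holds as a mismatch in specification: the protocol does not fix one primary model for its only primary outcome. That conclusion comes from the text and needs no assumption.

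The numerical stakes are modest and rest wholly on assumed inputs. With r from -0.1 to -0.4, the SE is about 0.5% to 8% lower with adjustment, and the estimate moves by about 0.1 to 0.3 kg at a 1-SE imbalance (0.14 to 0.57 kg at 2 SE). At an assumed true difference of 2 kg, the significance decision differs in about 2% to 7% of simulated comparisons. The calculations do not show that the unadjusted analysis would be invalid or materially inefficient. The passages should be aligned, but the mismatch does not undermine the trial.

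**What to change.** In the protocol's Statistical Analysis section, replace the ANOVA sentence with wording such as:

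*The primary analysis is an ANCOVA of 6-month weight change on study arm, with baseline weight as a prespecified covariate and a contrast for each pair of arms. The same model is used for weight change at the other time points.*

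Both additions to the bare model matter. The present sentence is the only statement of the pairwise contrasts and the only stated method for weight change at 6 weeks, 3 months and 12 months, so a replacement limited to the 6-month model would lose both.

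Then label the unadjusted ANOVA as a sensitivity analysis and the significance-screened ANCOVA as secondary or exploratory, and keep the synopsis in step.

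The cost is wording only. Weight is already measured at the baseline visit, so no new data are needed. The change should be dated before anyone sees results by arm.

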**Rationale for the current study**

Given the current popularity of the 5-2 diet, and the lack of data on its effectiveness, information is needed on whether it generates short-term weight loss and what is the most effective mode of its delivery, particularly in the community settings where standard approaches have low penetration and low efficacy.

A number of clients at our weight management programmes have reported their experience with the 5-2 diet and we have also piloted its use at our clinics. This identified some barriers such as finding suitable foods and planning meals for the fasting days, but the main hurdle to implementing the 5-2 diet is the hunger and discomfort on the fasting days. Our experience confirms that people who stick with the programme typically learn to tolerate the fasting days well, especially once they see the positive results. We now believe that although the diet in its usual self-help format can help some people, it is likely to be more effective if group support is included to assist adherence over the first few weeks. After this initial period, the diet should be much easier to maintain without further external support.

We propose to investigate the initial effects of the 5-2 diet delivered in two different formats (self-help and with group support), both of which are amenable for wide-spread use.

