**Study arm treatments**

**5-2 self-help (5-2 SH) arm** would receive a 20-minute session on the 5-2 plan and a written guide on how to use it with recommendations for internet resources along with a leaflet listing local resources for exercise. Participants will be encouraged to purchase and use pedometers to increase their exercise levels and to assess their weight weekly. In both 5-2 arms, participants will be asked to reduce their energy intake on two non-consecutive days per week to 500 calories for women and 600 calories for men. Participants will be seen by Research Health Psychologists.

**5-2 plus group support (5-2 GS) arm** would receive a brief explanation of the 5-2 plan and will be booked for six weekly group support sessions. Participants would also receive a leaflet listing local resources for exercise and will be encouraged to purchase and use pedometers to increase their exercise levels and to assess their weight weekly. The sessions will focus on helping clients to adhere to 5-2, share coping and fasting strategies and maintain motivation. Each session would last for approximately one hour and groups will comprise of 10-20 participants. Research Health Psychologists will run the groups.

**Standard advice self-help (SH) arm** would receive a 20-minutes session with an advisor focusing on healthy eating and physical activity and instructions on using the ‘Facts not Fads’ and the ‘Get Active, Stay Active’ British Heart Foundation self-help guides, supplemented by the NHS Change 4 Life series of booklets and a leaflet listing local resources for exercise. Participants will be encouraged to use pedometers to increase their exercise levels and to assess their weight weekly. Participants will be seen by Research Health Psychologists.

All sessions will be held at the Health and Lifestyle Research Unit, [name].

All participants will receive £20 for their travel and time at the 6 week and 6 and 12 month follow-up visits.

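### The planned ANOVA gives every pairwise weight comparison a variance averaged over three arms; if spread differs by arm, some confidence intervals will be too narrow and others too wide (optional fix, low severity)

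*Protocol*

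**What the plan says.** The Statistical Analysis section gives the method for weight change: "Weight change will be analysed by analysis of variance (ANOVA) with comparisons between all pairs of the three groups". It names no variance estimator and makes no provision for arms that differ in spread. In the primary analysis, missing weights are filled in "with participants lost to follow-up included as achieving no weight loss" (Synopsis, and again under Statistical Analysis). Carried-forward and completers-only analyses are added for comparison with other trials.

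The Sample Size section says "We aim to randomise 100 participants in each study arm". It gives no SD, effect size, alpha or power. The number is called pragmatic and justified as "large enough to provide reasonable confidence intervals on the key estimates". No dropout rate is given for any arm.

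Two arms start with a 20-minute session; the third has six weekly group sessions. The Rationale expects of the diet that "it is likely to be more effective if group support is included to assist adherence over the first few weeks". That is a statement about the mean, not the spread.

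**The concern.** It is often said that equal allocation makes a comparison of means robust to unequal variances. That holds for two arms. With three arms and one pooled variance it does not hold for the pairwise comparisons: the pooled standard error uses the average of three variances, while the true standard error of a difference depends only on the two arms compared. A wide third arm widens an interval it has no part in, and a narrow one shrinks it.

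The zero-change rule gives a concrete reason why spread could differ. Even if those who return have the same SD in every arm, the imputed arm variance depends on that arm's retention and mean loss. The protocol expects mean loss to differ, and retention may differ too.

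At stake is the calibration of the intervals, not the point estimates. That matters here because interval precision is the only stated basis for the sample size. The comparison of 5-2 self-help with standard advice also deserves a well-calibrated interval, since it compares the diet with advice at matched 20-minute contact.

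**Working it through.** **Inputs from the protocol.** 100 per arm in three arms (3 × 100 = 300, which agrees with the Synopsis); ANOVA with all pairs; missing weights set to zero change. There is no power calculation to reproduce.

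**Assumed inputs.** Two-sided 5% per comparison, and all SDs, mean losses and retention rates. Arms are ordered group support (GS) / 5-2 self-help / standard advice.

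**Formulas.**
- Pooled SE = √(2 × mean of the three variances / 100)
- True SE for arms i and j = √((SDi² + SDj²) / 100)
- Actual type I error = 2 × (1 − Φ(1.96 × pooled SE / true SE))
- Arm variance under zero imputation = r·s² + r(1 − r)·m², with retention r, completers' SD s and completers' mean loss m

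**Reference precision.** At SD 5 kg in every arm, the 95% half-width is 1.96 × 5 × √(2/100) = 1.39 kg.

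**Step 1: one arm with a different SD.** For 6/5/5 the variances are 36, 25 and 25, with mean 28.67.
- Pooled SE = √(2 × 28.67/100) = 0.757.
- True SE is √(61/100) = 0.781 for either GS comparison and √(50/100) = 0.707 for 5-2 self-help v advice.
- The ratios are 0.969 and 1.071, so the GS intervals are about 3% too narrow and the other about 7% too wide.

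| SDs (kg) | GS v 5-2 self-help | GS v advice | 5-2 self-help v advice | Power of the last* |
|---|---|---|---|---|
| 5/5/5 | 5.0% | 5.0% | 5.0% | 80% |
| 6/5/5 | 5.7% | 5.7% | 3.6% | 76% |
| 7/5/5 | 6.4% | 6.4% | 2.4% | 71% |
| 7.5/5/5 | 6.7% | 6.7% | 2.0% | 68% |
| 4/5/5 | 4.2% | 4.2% | 6.6% | 83% |

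*At the difference that gives 80% power with arm-specific variances.

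The last row shows the reversal: with GS the narrowest arm, its comparisons become conservative and the comparison of 5-2 self-help with advice becomes anti-conservative.

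**Step 2: zero imputation only.** Completers' SD is 6 kg in every arm and mean losses are 5/3/2 kg.
- Retention 85/70/60%: variances are 0.85×36 + 0.85×0.15×25 = 33.8; 0.70×36 + 0.70×0.30×9 = 27.1; 0.60×36 + 0.60×0.40×4 = 22.6. Pooled SE is 0.746, against true SEs of 0.780 (GS v 5-2 self-help) and 0.705 (5-2 self-help v advice). Type I error is 6.1% and 3.8%.
- Retention 80% in every arm: variances 32.8/30.2/29.4, giving 5.3% and 4.6%.
- Retention 70/80/85%: variances 30.5/30.2/31.1, which are practically equal, so every comparison stays near 5%.

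Over a wider grid (completers' SD 4 to 6 kg, mean loss 2 to 5 kg, dropout 15% to 40%), the GS comparisons ran at 4.8% to 6.1%. The remaining comparison ran at 3.5% to 5.3%, with power of 75% to 81%. At equal retention, the largest departures in that grid were 5.6% and 3.8%.

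**Step 3: does the remedy work?** In 40,000 simulated trials per setting, Welch tests held 4.9% to 5.2% on every comparison. Power for 5-2 self-help v advice was 79% to 80%. With equal SDs it was 79.9% by Welch and 80.0% pooled.

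**The case against.** The strongest objection is that the protocol never says the variance is pooled. It names a model and a set of comparisons, and a variance estimator is commonly left to the SAP, which is not shown. A Welch or HC3 choice there would be compatible with the protocol. This stands in part, and is a main reason for grading the point low. But ordinary ANOVA assumes a common residual variance, its standard pairwise comparisons use it, and nothing in the protocol allows for unequal spread.

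The second objection is that the protocol does not say spread will differ. That is correct. More contact might widen the spread of weight change or narrow it by making adherence more uniform.

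A reader might infer something stronger: that the group-support comparisons will be over-claimed and that 5-2 self-help v advice will lose power. The documents do not support this. It needs group support to be the widest arm, and no SD or retention figure says so. SDs of 4/5/5 reverse the pattern, and retention of 70/80/85% removes the imputation effect. More dramatic cases can be built: SDs of 7/5/4 give 7.8% for group support v 5-2 self-help and 1.8% for 5-2 self-help v advice. They assume a variance ratio of 49/16, about three, for which the protocol offers no basis.

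Third, the one route tied to the protocol's own text, zero imputation, moves the error rate by little more than one percentage point. That stands too.

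**Conclusion.** The point holds conditionally and at low severity. If the arms differ in spread, the usual ANOVA pairwise intervals will be miscalibrated in opposite directions despite equal arm sizes. Which comparison gains and which loses cannot be known from the protocol.

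Under the assumed inputs the likely size is modest. Zero imputation gives roughly 4% to 6% in place of 5% (3.5% at the extreme of the grid), with interval widths about 4% too narrow or 6% too wide in the 85/70/60% case. An SD ratio of 1.2 to 1.5 in one arm gives 5.7% to 6.7% for its comparisons and 3.6% to 2.0% for the other. The loss of power on the remaining comparison is the larger consequence, but only when one arm is clearly the widest. Point estimates are unaffected, and the protocol makes no power claim that could be breached.

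The change is worth making because it protects the intervals in whichever direction the spread differs.

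**What to change.** Add one sentence to Statistical Analysis: keep the linear model, and take every pairwise difference in weight change and its 95% CI from heteroscedasticity-consistent (HC3) standard errors, or from Welch tests where the analysis is unadjusted. Apply this to the primary, carried-forward and completers-only analyses. HC3 also fits the baseline-weight adjustment that the Synopsis describes; Welch does not.

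The cost is one sentence and one software option. If variances are equal, the Welch critical value is 1.972 on 198 degrees of freedom against 1.968 on 297, a widening of 0.2%. In an arm-only model, HC3 replaces s²/100 by s²/99 in each arm, a widening of √(100/99), or 0.5%.

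The change does not address two separate matters. Three unadjusted pairwise tests carry about a 12% chance of at least one false positive whatever the spread. The group-support arm is delivered in sessions where "groups will comprise of 10-20 participants", so outcomes there may be correlated within group, and neither method allows for that.

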**Secondary Outcomes**

1. Changes in weight, blood pressure, dietary habits, exercise levels and proportion of participants losing at least 5% of their body weight, at 6 weeks, 6 and 12 months and the self-reported change in weight at 3 months
2. Adherence to the three interventions, determinants of adherence, and barriers and facilitators to adherence.

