| **3 month follow up phone call**  Self-report weight; adherence to and ratings of 5-2 diet; recording of any concomitant weight management treatments | |  | **3 month follow up phone call**  Self-report weight; adherence to and ratings of 5-2 diet; recording of any concomitant weight management treatments | |  | **3 month follow up phone call**  Self-report weight; adherence to and ratings of the advice components; recording of any concomitant weight management treatments | |

| **6 month follow up**  Measurement of weight and blood pressure; adherence to and ratings of 5-2 diet; recording of any concomitant weight management treatments; change in eating habits; change in exercise levels (IPAQ) |  | **6 month follow up**  Measurement of weight and blood pressure; adherence to and ratings of 5-2 diet; recording of any concomitant weight management treatments; change in eating habits; change in exercise levels (IPAQ) |  | **6 month follow up**  Measurement of weight and blood pressure; adherence to and ratings of the advice components; recording of any concomitant weight management treatments; change in eating habits; change in exercise levels (IPAQ) |
| --- | --- | --- | --- | --- |

Pending their consent to continue in the study, participants will be followed up at 12-months (see the above 6 month follow-up for details of assessment).

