**Schedule of Assessment**

| **Time** | **Baseline** | **6 weeks** | **3 months** | **6 and 12 months** |
| --- | --- | --- | --- | --- |
| Demographics | X |  |  |  |
| Weight loss history | X |  |  |  |
| Weight | X | X | X (self-report) | X |
| Height | X |  |  |  |
| Blood pressure | X | X |  | X |
| Co-morbidities | X | X | - | X |
| Concurrent medications | X | X | - | X |
| International Physical Activity Questionnaire (IPAQ) | X | X | - | X |
| Diet Quality Questionnaire | X | X | - | X |
| Use of non-trial slimming methods | X | X | X | X |
| Feedback on treatment |  | X | - | X |
| Adherence to 5-2/advice |  | X* | X* | X* |
| Ratings of 5-2/advice |  | X** | - | X** |

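### The IPAQ and FFDBQ comparisons use ANOVA with no baseline term although both baselines are collected; adjusting for the baseline score would gain precision at no cost

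*Protocol*

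**What the plan says.** Section 9 of the protocol (Statistical Considerations, Statistical Analysis) gives one sentence to these two instruments: "IPAQ and FFDBQ scores in the three study arms will be compared using ANOVA". It does not say whether a score is the follow-up value or the change from baseline, and it names no covariate.

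Three other places bear on it:

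- **Secondary Outcomes (section 6)** defines the outcomes as "Changes in weight, blood pressure, dietary habits, exercise levels" and so on. The 6-month boxes of the Study Scheme Diagram also list eating habits and IPAQ exercise levels as changes.
- **Schedule of Assessment (section 8)** has the rows "International Physical Activity Questionnaire (IPAQ) | X | X | - | X" and "Diet Quality Questionnaire | X | X | - | X". The columns are baseline, 6 weeks, 3 months, and 6 and 12 months combined. The diet row is taken here to be the FFDBQ, because the Measures list has only one diet-instrument entry and it is headed with that name.
- **Baseline adjustment** appears only for weight. The Synopsis says "The primary analysis will compare weight loss between the three groups at 6 months, adjusting for baseline weight". The one ANCOVA in Statistical Analysis will "include any univariately significant variables in an analysis of covariance (ANCOVA) of weight change alongside study arm allocation", the candidate variables being age, socioeconomic grouping, baseline BMI and gender.

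**The concern.** Each participant completes both questionnaires before randomisation, and people differ widely and persistently in how they eat and exercise. Part of the spread in follow-up scores is therefore already known at baseline. An ANOVA by arm either ignores that information (if it analyses follow-up scores) or uses it with a fixed weight of one (if it analyses change). ANCOVA estimates the weight from the data.

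At stake are the width of the confidence intervals for the diet and exercise comparisons and how far a chance difference between arms at baseline shows up in the result. Precision is the protocol's own standard: Sample Size justifies the numbers by the confidence intervals they should give, not by power. Because the protocol itself names the method for these outcomes, this is a choice already made and not a detail left open for an analysis plan.

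**Working it through.** **Inputs from the protocol.** 100 participants randomised per arm (Sample Size); ANOVA with no baseline term (Statistical Analysis); both instruments measured at baseline, 6 weeks, 6 months and 12 months (Schedule of Assessment). No SD, correlation, power or precision figure is given for either instrument, so there is no stated figure to reproduce.

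**Assumptions.** Correlation r between baseline and follow-up of 0.3 to 0.6; equal SDs at the two times; no dropout. Results are in units of the score's SD.

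**Step 1: variance of a pairwise arm difference, relative to follow-up-score ANOVA.**

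- Follow-up scores: 1
- Change scores: 2(1 − r)
- ANCOVA on baseline: 1 − r²

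| r | Follow-up | Change | ANCOVA | Cut v. follow-up: r² | Cut v. change: 1 − (1 + r)/2 |
|---|---|---|---|---|---|
| 0.3 | 1 | 1.40 | 0.91 | 9% | 35% |
| 0.5 | 1 | 1.00 | 0.75 | 25% | 25% |
| 0.6 | 1 | 0.80 | 0.64 | 36% | 20% |

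The last column follows from (1 − r²)/[2(1 − r)] = (1 + r)/2. The gain rises with r on the first reading and falls with r on the second.

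**Step 2: 95% half-width with 100 per arm, 1.96 × √(2v/100), where v is the relative variance.**

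| r | Follow-up | Change | ANCOVA |
|---|---|---|---|
| 0.3 | 0.277 | 0.328 | 0.264 |
| 0.5 | 0.277 | 0.277 | 0.240 |
| 0.6 | 0.277 | 0.248 | 0.222 |

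To match ANCOVA, a follow-up-score ANOVA would need 100/(1 − r²) per arm: about 110, 133 and 156. Dropout widens every half-width but leaves the percentage cuts in step 1 as they are, because these do not depend on the sample size.

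**Step 3: chance imbalance.** The standard error of the baseline difference between two arms is √(2/100) = 0.141 SD. An imbalance of that size shifts the follow-up-score comparison by r × 0.141, which is 0.042, 0.071 and 0.085 SD at r = 0.3, 0.5 and 0.6. It shifts the change-score comparison the other way by (1 − r) × 0.141, which is 0.099, 0.071 and 0.057 SD. ANCOVA removes the shift. This is the precision loss of step 1 seen in a single trial, not a further loss.

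**Step 4: does the direction depend on the assumptions?** Against follow-up scores the gain is r², which is zero only at r = 0. Against change scores with unequal SDs s₀ (baseline) and s₁ (follow-up), the variance difference is (s₀² + s₁² − 2r·s₀·s₁) − s₁²(1 − r²) = (s₀ − r·s₁)², which is never negative. Apart from one degree of freedom for the covariate, ANCOVA is never the less precise choice. Only the size of the gain rests on r and on the SDs.

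**The case against.** The best reply is that the sentence can be read as an ANOVA of change scores. The words *raw* and *follow-up* do not appear in it, the outcomes are defined as changes, the preceding sentence speaks of changes in diet and exercise, and the same section analyses weight change by ANOVA. Against that, the section says *change* when it means it for weight and says *scores* here. The text does not settle the matter, so a contradiction between outcome and analysis is not proven. The precision point stands on both readings, because neither makes the baseline a covariate.

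A reader might go further and infer that the ANOVA does not estimate the stated outcome. That does not follow. Under randomisation the expected baselines are equal across arms, so the expected arm difference in follow-up score equals the expected arm difference in change. The analysis is unbiased for the right contrast.

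A reader might also infer that IPAQ totals are too skewed for ANOVA. The protocol defines no total score and gives no distribution, so this would rest on assumption alone. Nor is there a blood pressure analysis to correct: the protocol names none, and that may properly be left to the analysis plan.

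It is also fair to say that covariates for secondary questionnaires often belong in an analysis plan. Here, though, the protocol has fixed the method, so a plan that adds the baseline would depart from it.

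**Conclusion.** The point holds as one of efficiency. The stated ANOVA is valid and unbiased but less precise than the collected data allow, and it either leaves chance baseline imbalance in the comparison or over-corrects for it. ANCOVA on the baseline score would cut the variance by 9% to 36% if follow-up scores are meant, and by 35% to 20% if change scores are meant, as r goes from 0.3 to 0.6. That range for r and the equal SDs are assumptions; the direction of the gain depends on neither. Two secondary outcomes are affected. Weight, the 5% responder outcome and adherence are untouched, and no power claim or decision rule rests on the questionnaires, so the importance is modest.

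**What to change.** Replace the sentence in Statistical Analysis with:

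> IPAQ and FFDBQ scores at 6 weeks, 6 months and 12 months will be compared between the three arms by ANCOVA, with the participant's baseline score as covariate.

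The three time points are those at which the Schedule of Assessment has both questionnaires after baseline; the 3-month call has neither. The wording also removes the ambiguity about *scores*: with baseline in the model, analysing the follow-up value or the change gives the same estimated arm difference. The cost is one sentence in the protocol, with any analysis plan aligned to it. No extra data, visits or participants are needed.
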